### Interventions

Ad-MSC will be obtained from young healthy donors who previously gave their informed consent. Good manufacture practice (GMP)-accredited cell therapy laboratories from University of Navarra Clinic and from Salamanca University Hospital will be responsible of the master cell bank (MCB). MCB is the system whereby successive batches of the cell therapy product are manufactured by isolation and expansion of cells derived from a single adipose tissue sample. In this way, we ensure stability and uniformity in the treatment. MCB laboratories will send batches of cryopreserved cells to working GMP cell bank (WCB) laboratories. When a participant of the study is assigned to active treatment group, the sponsor will notify the assigned WCB laboratory to thaw and culture the cells in one passage. Finally, the batch will be packaged, labeled, and sent to the pharmacy service of the corresponding hospital (see Figs. 2 and 3). Three parallel groups have been designated as follows:
*Group 1*. Control group (*n* = 30). Placebo will consist of HypoThermosolFRS contained in an identical vial to that of the investigational medicinal product (IMP) and with the same volume.*Group 2*. Low-cell dose treatment group (*n* = 30). This group will receive a single intramuscular administration of 1 × 10^6^ cells/Kg weight.*Group 3*. High-cell dose treatment group (*n* = 30). This group will receive a single intramuscular administration of 2 × 10^6^ cells/Kg weight.

**Fig. 2 Fig2:**
[figure not shown]
Cell therapy product flowchart. From GMP laboratory to the patient. MCB, master cell bank; WCB, working cell bank; MSC, mesenchymal stromal cells. Ad-MSC are isolated from the adipose tissue sample and cultured at two passages until reaching a minimum dose of 250 × 10^6^ cells. Characterization of the cells and quality controls are established during the whole process. When a study subject is assigned to active treatment group, the sponsor notifies the assigned WCB laboratory to thaw and culture the cells in one passage. The batch is then packaged, labeled, and sent to the pharmacy service of the intended hospital. Manufacture process has been authorized by the Spanish competent authority (AEMPS), PEI number 15-103 Version 4:7/07/2019.

Regarding the allogeneic treatment presented in this protocol and possible risk of immune rejection, MSC are considered to have an immunoprivileged status. These cells display a low expression of MHC-HLA class I and are constitutively negative for HLA class II [28], thus avoiding the presentation of antigens to cytolytic T lymphocytes and immunological rejection. Furthermore, an autologous use would entail MSC isolation from multipathological patients. It has been suggested that the hyperglycemic environment and metabolic disorders associated with diabetes affect the biological properties and angiogenic capacity of cells [29–31]. Ad-MSC isolated from young healthy donors are more likely to present uniform cellular properties [7]. Treatment will be administered intramuscularly at the infrapopliteal level, at 25 points in the ischemic area parallel to the vascularization of the affected limb (Fig. 4). Treatment administration will be performed in the operating room, after patients have gone through mandatory presurgical assessment. As the IMP consists of a living drug, the importance of standardizing handling of Ad-MSCs was emphasized during the design of the clinical trial. Hence, a protocol for the management and administration of the medication was established. Doses are proposed according to previous experience of the group and bibliographical data. In previous trials (Phase I/IIa), 1 × 10^6^ cells/kg of patient weight have been used [7, 22, 32]. In parallel and considering the results of these tests, as well as the safety demonstrated in the administration of Ad-MSC, it seems justified to check whether a higher cell dose could improve the results obtained to date. In case of bilateral affection, the limb to be treated will be the more damaged one. In addition to the IMP administration and study procedures, patients will be managed according to routine clinical practice. Patients may voluntarily discontinue the study and will be withdrawn from the study if they present any clinically relevant condition that may represent a risk. After the end of the trial, patients will be managed according to best clinical practice.

**Fig. 4 Fig4:**
[figure not shown]
Once the targeted muscular injection points are selected (upper panel), repeated administrations of cell therapy are directly, easily, and minimally invasive administered into the lower part of the limb (lower panel)

### Outcome measures

#### Primary outcome measure

Safety will be assessed comparing the rate of treatment related complications between groups (proportion of treatment related complications among groups) at 24 h and 3, 6, and 12 months from treatment administration, including those related with anesthetic procedure, IMP administration and those occurring after the procedure.

#### Secondary outcome measures

Efficacy will be assessed through the following variables:

(a) Vascularity in the target limb will be assessed through mean change in percentage of vascular flow measured by MRI in the target limb at 12 months from baseline between groups. MRI will be centrally read by a blinded radiologist. (b) Disease severity will be evaluated through percentage of patients with an improvement in RB category at 3, 6, and 12 months from baseline [33] between groups. This scale is usually used in patients with chronic arterial disease to classify chronic arterial disease into clinical categories (category 0, asymptomatic; category 1, mild claudication; category 2, moderate claudication; category 3, severe claudication; category 4, pain at rest; category 5, minor tissue loss; category 6, ulcer o gangrene). (c) Ulcer healing (if any) will be assessed through the percentage of patients with a decrease in SVS-“WIfI” wound classification [34, 35] at 3, 6, and 12 months from baseline between groups. SVS-WIfI classification aims to be as functional in diagnosing PAD as the tumor-node-metastasis-based diagnosis system (TNM). Three measurable parameters are collected: wound (extension and depth), ischemia (blood flow), and foot infection (presence and extension). (d) PAD evolution will be evaluated by % of patients with an increase in ankle-brachial index at 3, 6, and 12 months from baseline between groups [36]. (e) Pain intensity will be assessed through mean change in visual analogue scale (VAS) from 0 to 10 cm, as described by the patient (0, absence of pain; 1–3, mild; 4–7, moderate; 8–10, severe) and percentage of patients with an improvement in pain intensity at rest at 3, 6, and 12 months from baseline between groups. (f) Percentage of patients with a decrease in temperature (°C), increase in gastrocnemius muscle perimeter (cm) and decrease in neuropathic symptoms of the treated limb compared with contralateral at 3, 6, and 12 months from baseline. (g) Mean change in percentage of amputations in each group at the end of the study will be registered.

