### Recruitment of eligible participants

Patients will be recruited by the attending clinicians (vascular surgeons) among the population of chronic, type 2 DM patients with peripheral arteriopathy that is usually under periodic follow-up in the outpatient clinic. Proposal to participate in the clinical trial will take place in one of these routine outpatient visits. Clinicians will explain to each subject the nature of the study, its purposes, procedures, expected duration, and the potential risks and benefits related to participation in the trial, as well as any inconvenience that this may entail. Patients will have enough time to read and understand the explanations before dating and signing the informed consent and will receive a copy of the signed document. Eligible patients will be (1) those aged between 40 and 90 years; (2) with type 2 DM diagnosed for more than one year; (3) with severe vascular arteriosclerosis, defined as Rutherford-Becker (RB) category 4 and 5 [23], mono or bilateral; and (4) with impossibility of surgical or endovascular revascularization or failure of revascularization surgery performed, at least 30 days before inclusion in the study. Patients with CLI and tissue loss in the target limb (RB category 6) or previous major amputation in the target limb will be excluded from the trial. Detailed eligibility criteria are described in ClinicalTrials.gov (NCT04466007). During trial conduct, periodic contacts with investigators and a trial newsletter are foreseen to assess possible difficulties in recruitment in advance and to keep investigator team informed of recruitment evolution. No specific methods to minimize attrition are foreseen. Eligible patients are severely ill patients that are usually adherent to medical visits, and thus a high drop-out rate is not expected.

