### Adverse events

An adverse event (AE), also referred to as an adverse experience, can be any unfavorable and unintended sign (i.e., an abnormal laboratory finding), symptom, or disease temporally associated with the use of a drug (or other investigational therapy) and does not imply any judgment about causality. An AE can arise with any use of the drug (i.e., off-label use, use in combination with another drug and with any route of administration, formulation, or dose, including an overdose). A suspected adverse reaction (SAR) means any AR for which there is a reasonable possibility that the drug caused the AE. An AE is considered “serious” if (SAE), in the view of either the principal investigator, if it results in any of the following outcomes: death of subject; event with risk to life, that is, there was an immediate risk of subject death at the time the reaction was observed; hospitalization or prolongation of hospitalization; persistent or significant disability/incapacity; congenital anomaly; or birth defect or any other significant medical condition, i.e., important AEs that do not pose an immediate risk to life and do not result in death or hospitalization but may endanger the subject or may require intervention to prevent one of the outcomes listed. A suspected adverse reaction is considered “unexpected” if it is not listed in the safety reference information for the IMP or is not listed at the specificity or severity that has been observed or is not consistent with previously available, known risk information.

Causality and severity assessment of any occurring AE will be performed by the principal investigator. AE will be registered from administration of IMP to end of study visit. Investigator will actively ask patients about AE occurrence in every study visit. Also, AE may be spontaneously reported by the patients. All of them will be appropriately registered in the patient medical records. Only AR and SAE will be registered in eCRF and reported according to legal requirements. For the purposes of this study, proportion of amputations in each study group is a secondary outcome and will be registered specifically, so notification as SAE will not be performed unless its clinical course is different of more severe than expected.

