#### Statistical analysis

Primary, secondary, and tertiary outcomes (safety, efficacy, and quality of life) will be assessed in intention to treat (ITT) and per protocol (PP) populations [39]. ITT population will include all patients who sign the informed consent and receive the investigational product. PP population will include patients who complete the 12-month follow-up period. A descriptive analysis of baseline characteristics of patients included in three groups will be performed. Quantitative variables will be expressed as mean and/or median and standard deviation and/or range. Qualitative variables will be expressed as percentages. When possible, the 95% confidence interval of each of the estimates made will be calculated. To analyze the primary outcomes, 24 h and 3, 6, and 12 months complication rates will be described and compared for the three groups using the Chi-square test or, if necessary, the Fisher exact test. The analyses of the secondary and tertiary outcomes will be performed as follows: qualitative variables will be described in terms of the percentage of improvement of the medical condition in each group and compared using the Chi-square test, or alternatively Fisher’s exact test. VAS scale, SF-12 scale, VascuQuol-6 scale, and the rest of the quantitative variables will be assessed by describing changes in variables at 3, 6, and 12 months from baseline, in an absolute and relative way. Changes at 3, 6, and 12 months in the three groups will be described and compared using the analysis of variance test, or the Kruskal-Wallis test, depending on whether or not the data follow a normal distribution. In all comparisons, a global comparison of the three groups and comparisons between groups by pairing will be carried out (low-dose treatment versus placebo, high-dose treatment versus placebo, high-dose treatment versus low dose, both treatment groups versus placebo). P values will be corrected by Bonferroni test. Regarding handling of missing data, a complete case analysis will be performed if percent of missing data is less than 5%. In another case, a data imputation will be performed for those variables with 25% or less missing values. Variables with more than 25% missing values will be removed from the analysis. The statistical analysis will be carried out by the statistical service of the Jiménez Díaz Foundation University Hospital. Data analyst will be blinded.

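### The Rutherford-Becker and ulcer outcomes count only improvement, so a patient who worsens is scored like one who stays stable

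*Protocol article*

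**What the plan says.** All places are in the protocol article.

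- **Entry (Recruitment of eligible participants).** Patients enter "with severe vascular arteriosclerosis, defined as Rutherford-Becker (RB) category 4 and 5". Category 6 is kept out: "Patients with CLI and tissue loss in the target limb (RB category 6) or previous major amputation in the target limb will be excluded".
- **Outcome (b) (Secondary outcome measures).** "Disease severity will be evaluated through percentage of patients with an improvement in RB category at 3, 6, and 12 months from baseline". The categories are labelled "category 4, pain at rest; category 5, minor tissue loss; category 6, ulcer o gangrene".
- **Outcome (c) (same section).** "Ulcer healing (if any) will be assessed through the percentage of patients with a decrease in" the WIfI wound classification, at the same three time points. On the classification itself: "Three measurable parameters are collected: wound (extension and depth), ischemia (blood flow), and foot infection (presence and extension". The text does not say which of the three must fall.
- **Analysis (Statistical analysis).** For secondary and tertiary outcomes, "qualitative variables will be described in terms of the percentage of improvement of the medical condition in each group", compared by chi-square or Fisher's exact test, with Bonferroni-corrected p values.
- **Adverse events.** "Only AR and SAE will be registered in eCRF and reported according to legal requirements".
- **Table 1.** WIfI is marked at the selection visit and at 3, 6 and 12 months, with no restriction to patients who have an ulcer. RB category is marked at the selection visit only.

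**The concern.** Patients enter at RB 4 or 5, so the RB steps in the wrong direction open to them are 4 to 5, 4 to 6 and 5 to 6. Outcome (b) scores each of these as not improved, which is also the score of a patient who did not move. Outcome (c) has no place for a wound that appears or deepens. A patient ulcer-free at entry is either outside its denominator or, if the wound grade is what must fall, a fixed non-responder.

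The trial's name stands for no more amputations, and new tissue loss is a step in that direction. Two misreadings become possible on (b) and (c). A product that prevents progression without reversing disease shows nothing. A product that helps some patients and harms others shows its benefit there without the harm beside it.

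**Working it through.** **Step 1. Where each kind of worsening is counted**

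| Event in the target limb | Outcome (b) | Outcome (c) | Elsewhere |
|---|---|---|---|
| RB rises (4 to 5, 4 to 6, 5 to 6) | not improved, same as stable | not applicable | indirectly, through mean change in MRI flow, VAS and quality of life |
| New ulcer, ulcer-free at entry | at most not improved | outside the denominator, or not improved | as an event only if an adverse reaction or serious |
| Higher wound grade | at most not improved | not improved, same as stable | as above |
| Amputation | not addressed | not addressed | outcome (g) |

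A new ulcer judged non-serious and unrelated to treatment is not entered in the eCRF as an adverse event. It is also not a treatment-related complication under the primary outcome. As an event, it enters no planned count.

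**Step 2. Size, by illustration**

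The plan gives no effect size, power or alpha to reproduce. From the documents: 30 patients per arm, a chi-square test on the percentage improved, and Bonferroni over four pairings. Assumed: all rates below, two-sided alpha 0.05, and 0.05 / 4 = 0.0125 after correction.

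Method: sum the binomial probabilities of all pairs of counts (0 to 30 in each arm) for which the uncorrected Pearson chi-square exceeds its critical value. As a check, the normal approximation is power = Φ[(d − z·se0) / se1], where d is the difference in proportions, se0 = √(2·p̄(1 − p̄)/30), se1 = √(p1(1 − p1)/30 + p2(1 − p2)/30), and z = 1.960 or 2.498.

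*Case 1: progression is prevented.* Control 30% worse, 40% same, 30% better; treated 10% worse, 60% same, 30% better.

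- Improved-only test, 30% v 30%: rejects 4.9% at 0.05. This is the test's own error rate.
- Worsened percentage, 30% v 10%: p̄ = 0.20, se0 = 0.1033, se1 = 0.1000. At 0.05, (0.20 − 1.960 × 0.1033) / 0.1000 = −0.02, so Φ = 49%; exact 50%. At 0.0125, (0.20 − 2.498 × 0.1033) / 0.1000 = −0.58, so Φ = 28%; exact 29%.

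*Case 2: more improve and more worsen.* Control 10% worse, 60% same, 30% better; treated 30% worse, 20% same, 50% better.

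- Improved-only test, 30% v 50%: p̄ = 0.40, se0 = 0.1265, se1 = 0.1238. At 0.05, (0.20 − 1.960 × 0.1265) / 0.1238 = −0.39, so Φ = 35%; exact 35%. At 0.0125, (0.20 − 2.498 × 0.1265) / 0.1238 = −0.94, so Φ = 17%; exact 18%.
- The tripling of worsening, 10% to 30%, has no effect on that result.

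The Case 1 result does not depend on the rates chosen. If the improvement rates are equal, no difference in worsening, of whatever size, can move the improved-only test.

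**Step 3. What the fix can show at this size**

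For 30% v 10% worsened, the 95% interval for the difference is 0.20 ± 1.96 × 0.1000, or about 0 to 40 percentage points.

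**The case against.** Responder percentages are an ordinary choice for secondary outcomes of preliminary efficacy in a phase II trial whose primary outcome is safety. Nothing in the article forbids tabulating worsened patients, and shift tables are often left to an analysis plan, which is not shown here. This limits the weight of the point. It does not remove it, because the article states the scoring rule for (b), (c) and the analysis, and that rule counts improvement alone.

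Three stronger readings are tempting, and the documents do not support them.

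- *That progression short of amputation shows in no efficacy comparison.* Mean change in MRI flow, VAS and the quality-of-life scores moves in both directions and is compared between arms. New ulceration or gangrene that leads to hospitalization, or otherwise meets the seriousness definition, enters the eCRF as a serious adverse event. What is missing is a count of RB rises, new ulcers and higher wound grades.
- *That patients entering at RB 4 cannot be scored on the ulcer outcome, so that a known share of the 90 has no ulcer score.* Table 1 schedules WIfI for everyone, the RB 4 share is not given, and a fall in the ischemia component might count as a decrease. The component and the denominator are open, not settled against these patients.
- *That a new ulcer is simply a move from RB 4 to RB 5.* The article's own labels put ulcer in category 6, which eligibility excludes, while (c) allows for ulcers at baseline. The text must be reconciled before an ulcer can be mapped to a category.

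It is also fair to say that the rates in the illustration are chosen, and that the 35% in Case 2 falls to 18% once a Bonferroni correction over four pairings is applied.

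**Conclusion.** The point holds for outcomes (b) and (c). As written, they and the planned analysis do not separate worsening from stability, and patients ulcer-free at entry may drop out of (c). With equal improvement, the planned comparison on (b) stays at its error rate of about 5% whatever happens to progression. Under the assumed rates, comparing 30% with 10% worsened directly would detect the difference about 50% of the time at 0.05 and 29% at 0.0125. In the mixed case, the improved-only test would declare benefit 35% or 18% of the time at the same two levels, with worsening tripled and unreported on that outcome.

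The structural part rests on the text alone. The percentages rest on the assumed rates, on 30 evaluable patients per arm and on the assumed alpha levels. These are secondary outcomes, so the effect is on how efficacy is interpreted, not on the primary safety comparison. The change should be made.

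**What to change.** 1. In Secondary outcome measures (b) and in Statistical analysis, keep the percentage improved. Beside it, report the percentages improved, unchanged and worsened by arm at 3, 6 and 12 months, with 95% confidence intervals for the differences.
2. In (c), state that the wound grade is meant, and define the denominator for healing. Add, for all treated patients including those ulcer-free at entry, the percentage with a new target-limb ulcer or a higher wound grade.
3. State that any claim of benefit on (b) or (c) is read beside the worsened percentage.
4. Reconcile Table 1, which marks RB only at the selection visit, with the 3-, 6- and 12-month assessments that (b) needs.
5. Reconcile the labels of RB categories 5 and 6 in Secondary outcome measures with the eligibility text in Recruitment of eligible participants.

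**Cost.** The WIfI part needs wording only, since the assessments are already scheduled at 3, 6 and 12 months. The RB part depends on item 4, but (b) already requires that follow-up as it stands. The downside is a few more percentages to report, with wide intervals at 30 per arm (about ±20 points in the example above).

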## Methods

### Study design

This is a study protocol of a multicenter, randomized, placebo-controlled, double-blinded, dose-finding, phase II clinical trial of three parallel groups to evaluate safety and efficacy of the intramuscular administration of allogeneic Ad-MSC in diabetic patients with CLI and without possibility of revascularization, over conventional treatment. The overall study design is reported according to the CONSORT statement and agrees with the SPIRIT 2013 checklist.

A total of 90 eligible patients will be recruited from ten academic hospitals in Spain (Jimenez Diaz Foundation University Hospital, La Paz University Hospital, Navarra University Clinic, Gregorio Marañón General University Hospital, Virgen de la Arrixaca University Clinical Hospital, Salamanca University Hospital, Victoria Eugenia-Cruz Roja Española Hospital, La Fe Clinical and Polytechnic University Hospital, Valladolid Clinical University Hospital and Alicante General University Hospital). Participants will be randomly assigned into control group, low-cell dose treatment group, or high-cell dose treatment group, at a ratio 1:1:1.The flowchart of the trial is presented in Fig. 1 and the study procedures schedule is shown in Table 1. Recruitment period will last 1.5 years, and follow-up period will be 1 year. The expected total duration of the study, from the first visit of the first patient to the last visit of the last patient, will be 2.5 years.

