**Fig. 1 Fig1:**
[figure not shown]
Flowchart: 90 patients will be recruited in the study and randomly allocated to three groups (high-dose group = 30; low-dose group = 30; control group = 30). The assessment will be done 24 h and 3, 6, and 12 months, respectively

**Table 1 Tab1:** Schedule of study procedures

	Study period						
	Enrolment		Treatment	Follow-up			
Timepoint	***V-1, selection visit***	***V0, baseline visit***	V1, treatment	***V2, 24 h***	***V3, 3 m***	***V4, 6 m***	***V5, 12 m***
	***Day − 30 to day − 21***	***Day − 20 to − 1***	Day 0	***Day 1***	***Day + 90 ± 7***	***Day + 180 ± 15***	***Day + 365 ± 15***
***Eligibility criteria***	X	X					
***Informed consent***	X						
***Anamnesis***	X						
***Physical examination***	X		X	X	X	X	X
***Blood test***	X				X	X	X
***Urine pregnancy test***	X						
***Rutherford-Becker category***	X						
***Ankle-arm index***	X				X	X	X
***Ulcers evaluation (Wifi classification)***	X				X	X	X
***VAS scale***	X			X	X	X	X
***Gastrocnemius muscle perimeter***	X				X	X	X
***Temperature of the limb***	X				X	X	X
***Neuropathic symptoms***	X				X	X	X
***Quality of life scales (SF-12 and VascuQol-6)***	X				X	X	X
***MRI***	X						X
***Randomization***		X					
***Pre surgical evaluation***		X					
***Treatment administration***			X				
***Concomitant medication***	X	X	X		X	X	X
***Adverse events***			X	X	X	X	X

*MRI* magnetic resonance imaging, *h* hours, *m* month, *v* visit

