### Blinding, randomization and allocation concealment

Masking of participants will be guaranteed as follows: the solution for intramuscular infusion of Ad-MSC (active treatment) will have the same aspect as HypoThermosolFRS (placebo), and the syringes will be identified by a label that will exclusively contain the information corresponding to the clinical trial and the patient code. However, since the density of each product may be different, it is assumed that there is a risk that the clinical investigator administering the treatment may know which treatment is being applied. For that reason and to ensure double blind, each center will count, as a minimum, with two investigators per enrolled patient: a non-blinded investigator who will administrate cellular therapy and a blinded investigator who will perform the assessment of participants as described in Table 1. Randomization will be performed through the electronic case report form (eCRF). Study subjects will be assigned to group 1, 2, or 3, at a ratio 1:1:1, based in a random block sequence prepared by the sponsor’s statistical service. The assigned group information from each participant will not be visible in the eCRF. Then, an email with the assigned treatment group information of the participant will be sent automatically to non-blinded team. No stratification process has been designed in the randomization scheme. If a phase III clinical trial is subsequently developed, stratification will be defined, according to preidentified factors that could influence efficacy outcomes. During the study, masking can be broken in the event of a serious adverse event (SAE) related to the study medication that requires urgent medical treatment. The researcher will notify the sponsor within a maximum period of 24 h and sign the SAE notification form that will be sent by fax or email to the person in charge of pharmacovigilance of the study. The sponsor will communicate to the investigators any information that may affect the safety of the trial subjects as soon as possible. In the event of unmasking, blinding will be maintained for those responsible for evaluating the primary variable and for those responsible for data analysis and interpretation of the results.

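### Rutherford-Becker category is a secondary efficacy outcome at 3, 6 and 12 months, but Table 1 schedules it only at the selection visit

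*Protocol article*

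**What the plan says.** The protocol article, Secondary outcome measures (b), evaluates disease severity by the "percentage of patients with an improvement in RB category at 3, 6, and 12 months from baseline", between groups. The Statistical analysis section compares qualitative outcomes of this kind across groups by the Chi-square or Fisher exact test.

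The Study design section states that "the study procedures schedule is shown in Table 1". The Blinding section relies on the same table: each centre has "a blinded investigator who will perform the assessment of participants as described in Table 1". In Table 1 the row "Rutherford-Becker category" has one mark, at V-1.

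On the scale itself, the Recruitment section admits RB categories 4 and 5. Its exclusion sentence begins "Patients with CLI and tissue loss in the target limb (RB category 6". Outcome (b) prints the upper end of the scale as "category 5, minor tissue loss; category 6, ulcer o gangrene".

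**The concern.** The outcome needs a baseline category and a category at each of three later visits. The printed schedule supplies only the baseline, and that single mark is what one would expect if RB category were used for eligibility alone. The article does not leave the timing to a fuller document. It states the timing twice, and the two statements disagree.

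At stake is the one outcome that the article labels as disease severity. The Discussion also cites a decrease in RB category as part of the efficacy evidence from the earlier pilot study of autologous cells, so its loss would remove a direct link to the trial's rationale. A category that was not rated at a follow-up visit cannot be recovered later as a prospective blinded rating.

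The wording of categories 5 and 6 is a secondary matter. The same scale decides who enters and who counts as improved, so it should be described in one way throughout.

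**Working it through.** No sample size, power or alpha figure is involved. The check sets the outcome time points against the marks in Table 1.

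**1. Time points required and scheduled**

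| Measure | Follow-up time points in the outcome text | Marks in Table 1 | Agree? |
|---|---|---|---|
| RB category | 3, 6, 12 months | V-1 | No |
| Ankle-arm index | 3, 6, 12 months | V-1, V3, V4, V5 | Yes |
| WIfI | 3, 6, 12 months | V-1, V3, V4, V5 | Yes |
| VAS | 3, 6, 12 months | V-1, V2, V3, V4, V5 | Yes |
| Gastrocnemius perimeter, temperature, neuropathic symptoms | 3, 6, 12 months | V-1, V3, V4, V5 | Yes |
| SF-12 and VascuQoL-6 | 3, 6, 12 months | V-1, V3, V4, V5 | Yes |
| MRI | 12 months | V-1, V5 | Yes |

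V3, V4 and V5 are the 3-, 6- and 12-month visits. RB category is the only efficacy or quality-of-life measure with its own row whose marks do not match its outcome.

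**2. Could this be a text-extraction fault?** It is unlikely. The rows next to it, "Ankle-arm index" and "Ulcers evaluation (Wifi classification", keep their column alignment, and the RB row has one mark followed by empty cells.

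**3. Size, if Table 1 is followed as printed**

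- Required follow-up ratings: 3 per patient × 90 patients = 270.
- Scheduled: 0 per patient × 90 patients = 0.
- Missing by schedule: (270 − 0) / 270 = 100%.

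**4. Effect of the missing-data rule.** The Statistical analysis section allows imputation for variables with 25% or less missing and removes those with more than 25% missing. Since 100% > 25%, outcome (b) would be removed and imputation would not apply.

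**5. Could RB category be derived from what is scheduled?** Physical examination, VAS and WIfI are marked at V3 to V5 and bear on rest pain and wounds. The article gives no derivation rule. The printed scale defines categories 1 to 3 by the severity of claudication, and Table 1 has no claudication row. A category 4 patient who improves could fall into any of those categories, so the scheduled rows do not fully replace a rating.

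**6. Categories 5 and 6**

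| Place | Category 5 | Category 6 |
|---|---|---|
| Recruitment section | Eligible; no description | Excluded; described as tissue loss |
| Secondary outcome (b) | Described as minor tissue loss | Described as ulcer or gangrene |

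Tissue loss is thus attached to the excluded category in one place and, qualified as minor, to an eligible category in the other. By the printed labels an ulcer belongs to category 6, while outcome (c) measures ulcer healing where there is an ulcer.

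**The case against.** The strongest reply is that outcome (b) itself prescribes RB category at 3, 6 and 12 months. On that view there is an assessment plan, and the table merely omits three marks. The visits exist, related examinations take place at them, and a site that reads the outcome text would record the category. The full protocol and the eCRF are not shown and may already include it. Only one of seven groups of secondary outcomes is affected, efficacy is described as preliminary, and no sample size rests on RB category.

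Much of this stands. A reader might infer that the outcome cannot be computed at all, or that 270 assessments will in fact be missed. The article does not support either: the count describes the marks in the printed table, not what sites will do. What remains is that two parts of the article disagree, and that the Blinding section points the assessor to the part that lacks the measure.

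On categories 5 and 6, the reply is that eligibility is given by number (4 and 5 in, 6 out), which fits the order of the scale; that the scale is a cited one applied by vascular surgeons; and that detailed criteria are left to the registry. This also has force. A reader might infer that every patient with an ulcer is excluded, or that sites will score the same ulcer differently. The first takes an abbreviated label literally, and outcome (c) applies only where there is an ulcer. The second is speculation. The mismatch in wording is real, but its consequences are not shown.

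**Conclusion.** The inconsistency holds. Outcome (b) needs three follow-up RB ratings per patient and Table 1 schedules none. If the table is followed as printed, there are no follow-up RB data, no stated way to derive them, and the article's own missing-data rule removes the outcome.

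This rests on one assumption, that sites work from Table 1 rather than from the outcome text. The article says that the assessor does, but the full protocol or eCRF may already provide for RB category at follow-up. In that case only the published table needs correction. The effect is confined to one secondary outcome; the primary safety outcome does not depend on it. It is most likely an omission from the table rather than a deliberate choice, but it should be corrected because the remedy is simple and missed ratings cannot be recovered.

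The wording of categories 5 and 6 is a separate, lesser inconsistency. The passages must be reconciled; this review takes no position on which wording is right.

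**What to change.** - In Table 1, mark RB category at V3, V4 and V5, as for the ankle-arm index and WIfI. The Blinding section already assigns Table 1 assessments to the blinded investigator, so no further text on the rater is needed.
- Confirm that the eCRF captures RB category at those three visits, and add the field only if it is absent.
- If follow-up ratings are not intended, revise outcome (b) instead, so that the two places agree.
- Reconcile the descriptions of categories 5 and 6 between the Recruitment section and outcome (b).

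The cost is three marks in one table row, a check of the eCRF and one wording correction. No visit is added, and the rating is made at visits where the limb is already examined.
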